### 2.6. Outcomes

The primary outcomes are 0-to-100 VAS for low back and leg pain. The secondary outcomes are Oswestry Disability Index (ODI); EQ-5D; Roland-Morris Disability Questionnaire (RMDQ); Oxford Claudication Score (OCS); physical function tests, including treadmill tests, assessment of the walking duration, and distance without leg pain; radiologic testing; and adverse events. Every outcome variable will be assessed before and after treatment, and follow-up will continue for up to 6 months in all groups (Table 1).

Zero-to-100 VAS for average low back and leg pain during last week will be assessed once a week during the participating treatments. Arithmetic mean of the peak pain and lowest pain, which the patient experienced during last week regardless of position and activity (walking/standing), will be used as the average VAS score for low back and leg pain. If the patient has pain in both legs, the scores from the more severe side will be recorded. ODI is a widely used tool for assessing the disability related to low back pain. It consists of ten dimensions, such as the pain severity, ability for self-care, lifting, walking, standing, sitting, traveling, sexual function, and sleep quality. Each dimension can have 1 to 6 scores and the ODI can be calculated through the total sum of scores multiplied by 100 and divided by the numbers of answered dimensions. In addition, individual scores of 10 items will be assessed as well. The validated Korean version of ODI will be used in this study [15]. The EQ-5D will be evaluated to assess the quality of life; it has five questions that assess the respondent's mobility, self-care, daily activities, pain, and anxiety/depression, which can have scores of 1 to 3. Patients will have a five-digit number combination, which represents the quality of life. A validated Korean EQ-5D will be used for this study [16]. RMDQ is a tool for assessing the functional status of patients with low back pain. It has 24 questions, and each has yes/no options. The RMDQ score is calculated through adding all questions that are checked as yes so that it ranges from 0 (no functional limitation) to 24 (worst condition). The validated Korean version will be used for this study [17]. The OCS is a tool for evaluating the claudication severity and leg symptoms, which are the most bothersome problems for the patients with LSS. Ten questions related to three dimensions, including pain, ischemic symptoms, and physical symptoms, can have a score of zero (no symptoms) to 5 (worst symptoms), and they can be presented with the percentage of the possible maximum score. Because the RMDQ does not have validated Korean version, we will use a tentatively translated version [18]. To assess the physical function of the patients, the treadmill and walking tests will be evaluated. In this treadmill test, patients walk on a flat treadmill at a speed of 1.5 miles/sec until they complain of leg pain. For the walking test, patients will be ordered to walk on a 50 m flat track at a comfortable pace, and the time until leg pain starts will be recorded. Radiologic testing, including L-spine MRI and X-ray flexion and extension views, will be conducted to evaluate the condition of the spinal canal with stenosis and lumbar spine instability. For patients with spondylolisthesis, changes in the spinal instability will be evaluated. In addition, the AP diameters between pre- and posttreatment will be evaluated to check on the structural changes. The types and frequency of additional treatments usage during follow-up period will be assessed and analyzed after the end of the study. Adverse events (AEs) related to treatments will be monitored by the physicians, and patients should report any unexpected signs or symptoms during the treatment. AEs will be appraised using Spilker's classification, and the types and frequency will be analyzed. Outcome assessors will be open to the allocation results of the participants.

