
### 2.7. Feasibility Assessment

Recruitment rate and dropout rate during the study period will be assessed for evaluating the feasibility of the study design. Reasons for the dropouts will be analyzed. Compliance to the offered treatment interventions and outcome assessment will be evaluated based on the compliance rate of participants as well as qualitative analysis on the outcome assessors' experiences. For future full-scaled RCT, we will calculate sample size based on the study result.

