### 2.8. Statistical Analysis

Statistical analysis will be conducted on the basis of intention-to-treat analysis (ITT). Missing values will be imputed by the last observation carried forward (LOCF) method. Baseline characteristics will be presented as the mean and standard deviation (SD) for continuous outcomes and as the frequency for categorical outcomes. Statistical analysis between groups will be conducted with a *t*-test (Wilcoxon rank sum test in case of nonnormal distribution data) or a chi-square test, respectively. Primary and secondary outcomes will be analyzed with analysis of covariance (ANCOVA), with the change in the outcome scores between the groups as the dependent variable, baseline scores as a covariate, and study groups as a fixed factor. Pre- and posttreatment differences in each group will be analyzed with a *t*-test (Wilcoxon rank sum test) or a chi-square test. Repeated measures analysis of variance will be conducted to identify the trend in data. The frequency of AEs in each group will be compared using Fisher's exact test. The types of AEs will be assessed through qualitative analysis.

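### The ODI formula in section 2.6 leaves the maximum item score out of the divisor, so taken literally it runs from 100 to 600 and is not a percentage

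*Protocol article*

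**What the plan says.** Section 2.6 of the protocol article (Outcomes) describes the ODI as follows. On its structure: "It consists of ten dimensions". On item coding: "Each dimension can have 1 to 6 scores". On the index: "the ODI can be calculated through the total sum of scores multiplied by 100 and divided by the numbers of answered dimensions". It gives no range for the resulting score and no second formula. It adds that "The validated Korean version of ODI will be used in this study", with a citation, but does not reproduce that version's scoring key.

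For the Oxford Claudication Score (OCS), also ten items but coded 0 to 5, the same section says that "they can be presented with the percentage of the possible maximum score". For the Roland-Morris questionnaire it states the range, 0 to 24.

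The ODI is one of several secondary outcomes. Table 1 schedules it at seven time points (weeks 2, 3, 4, 5, 6, 18 and 30). Section 2.8 analyses primary and secondary outcomes by ANCOVA on the change score with baseline as covariate. On the use of the pilot data, section 2.7 says: "For future full-scaled RCT, we will calculate sample size based on the study result".

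**The concern.** Multiplying by 100 turns a proportion into a percentage. The printed quotient is not a proportion: the sum of item scores divided by the number of items answered is the mean item score, which lies between 1 and 6. The term that would make it a proportion, the maximum or span of an item, is missing. This is a scoring rule that is stated and stated wrongly. It is not a detail that the article leaves to a fuller document.

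What is at stake is how ODI results are reported and reused. A pilot's means, SDs and differences are what later readers and planners take from it. If they are published on an undeclared 100-600 scale, they cannot be set beside ODI values on a 0-100 scale without conversion, and nothing in section 2.6 warns that conversion is needed.

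**Working it through.** **Inputs, all from section 2.6:** 10 items; item scores 1 to 6; index = 100 x S / n, where S is the sum of the answered items and n the number answered. The document states no ODI range, so there is no figure of its own to reproduce.

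**Range of the printed rule**

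- All items at 1, n = 10: 100 x 10 / 10 = 100.
- All items at 6, n = 10: 100 x 60 / 10 = 600.
- With n = 8 or 9 the limits are the same, because n cancels: 100 x (1 x n) / n = 100 and 100 x (6 x n) / n = 600.

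**Does another item coding rescue the rule?** With items coded 0 to 5 and the same divisor, the range is 0 to 100 x 5n / n = 500. It does not.

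**Relation to a 0-100 score.** Subtract the minimum and divide by the span:

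P = 100 x (S - n) / (5n) = 20 x S/n - 20, which is 0 when all items are 1 and 100 when all are 6.

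Hence printed score = 100 x S/n = 100 + 5P, for any n.

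| P (0-100) | Printed score |
|---|---|
| 0 | 100 |
| 40 | 300 |
| 60 | 400 |
| 100 | 600 |

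In a change score the constant 100 cancels, so changes, group differences, SDs and confidence limits for differences are 5 times those on the 0-100 scale.

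**An alternative percentage.** Dividing by the maximum alone, 100 x S / (6n), runs from 100/6 = 16.7 to 100. The printed values are then 6 times as large. The factor of 5 therefore belongs to the rescaling that starts at zero.

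**What does not change.** The relation is linear and increasing, with the same constants for every patient and every n. A simulated data set of 36 patients in three groups of 12 (invented item scores, not trial data), analysed by ANCOVA on change with baseline as covariate, showed this:

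| Quantity | Printed scale | 0-100 scale |
|---|---|---|
| Baseline mean | 409.4 | 61.9 |
| Baseline SD | 45.2 | 9.05 |
| One adjusted group difference | 100 | 20 |
| Overall group p-value | 5.6e-12 | 5.6e-12 |

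**Sample size for a later trial.** The number per arm depends on (SD / difference) squared. With illustrative values that are not in the document:

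- Difference 10, SD 20 (both on 0-100): 63 per arm.
- Difference 50, SD 100 (both on the printed scale): 63 per arm.
- Difference 10 on 0-100 with SD 100 on the printed scale: 1570 per arm, since the ratio is 5 times as large and 5 squared = 25.

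Only the mixed case goes wrong.

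**The case against.** The best defence is that this is a unit error with no inferential effect. The printed score is an exact, reversible function of the percentage score; ANCOVA, t-test and rank-test p-values for the groups are the same on either scale; and section 2.6 keeps the individual item scores, so anyone can convert afterwards. No eligibility, stopping or decision rule uses an ODI value. All of this stands, and it limits the severity.

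A second defence is that the article names a validated Korean version, whose own key may be what the trial applies. The printed sentence would then be a paraphrase that lost a term. That is possible and cannot be checked here. It makes the harm conditional, but it does not make the sentence right, because the printed formula is the only ODI scoring rule in the document.

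Three stronger readings are tempting and are not supported:

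- *Every ODI result of the trial will be on a false scale.* This holds only if the sentence is applied literally.
- *The future trial's sample size will be inflated 25-fold.* This needs an SD from one scale and a target difference from the other. The document plans nothing of the kind: it states no important difference for the ODI, section 2.7 does not name the ODI as the basis for sample size, and the primary outcomes are the 0-to-100 VAS scores. A baseline mean around 400 would also be noticed by anyone expecting 0-100.
- *The document implies 0-5 items for the ODI.* It states 1 to 6. The 0-5 coding is given for the OCS, a different instrument.

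**Conclusion.** The formula is wrong as written. With the stated item coding it yields 100 to 600, no item coding turns it into a percentage, and nothing elsewhere in the article corrects it. If applied literally, ODI means would be 100 plus 5 times their 0-100 values, and SDs, differences and the confidence limits of differences would be 5 times as large. Tests and standardised effects would be unaffected.

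The size rests on two assumptions: that the sentence is used as the scoring rule, and that the intended scale is 0-100 starting at zero. Under a percentage of the maximum with 1-to-6 items the factor would be 6. For a secondary outcome in a pilot of 36 patients, with a reversible error and no planned mixing of scales, the severity is moderate to minor. It should be corrected before any ODI value is reported.

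**What to change.** Replace the formula sentence in section 2.6, and the matching line of the scoring program, with one rule:

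- items coded 1 to 6: ODI (%) = 100 x (sum of answered items - number answered) / (5 x number answered);
- equivalently, items recoded 0 to 5 by subtracting 1: ODI (%) = 100 x sum / (5 x number answered).

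State the range, 0 to 100. Before adopting the rule, confirm that item coding, divisor and range match the scoring key of the cited validated Korean version. If any ODI values have already been computed by the printed rule, convert them with P = (printed score - 100) / 5.

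The cost is one sentence and one line of code, plus a check of the key. Data collection and patients are not affected.

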### 2.5. Intervention

Patients will be allocated into one of three groups, the MT 1, MT 2, or usual care groups, during four weeks in the inpatient unit. Patients in the MT 1 group will receive integrative treatments, including herbal medications, Chuna, acupuncture, and patient education. Those in the MT 2 group will receive Chuna, acupuncture, and patient education without herbal medication. Those in the usual care group will be offered conventional nonsurgical treatments with analgesics, epidural steroid injection, and physiotherapy. Any concomitant therapies for lumbar stenosis will be prohibited during the four-week treatment period in all patients.

In the MT 1 group, herbal medication (Gang-Chuk Tang) will be offered during the participation period. Gang-Chuk Tang (110 g), which is an herbal decoction agent consisting of* Eucommiae Cortex, Achyranthis Radix, Cibotii Rhizoma, Sorbus commixta, Geranium thunbergii, Saposhnikovia Radix*, and* Acanthopanacis Cortex*, will be administered three times a day for four weeks. Chuna is a specific manipulation technique in Korean medicine, which consists of mobilization within the limits of passive range of joint motion and muscle relaxation according to the patient's respiration [13]. In this study, we will perform relaxative Chuna using Ergo style TM FX.-5820 Table (Chattanooga Group, USA); the detailed methods are presented in the following list. 

*Steps for the Chuna Technique*

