The patients are to relax in bed, because of the possibility that they will experience symptoms in the incubation period that they might not feel prior to the treatment during the first week of treatment.From the second week of the treatment, the patients must practice simple movements such as moving the lower limbs, head, or shoulders slightly to the left and to the right according to the instructions of the medical team. In particular, it will be necessary to compare the symptoms patients experience for a week of treatment on a weekly basis. In addition, the patients should be able to accurately compare and be aware of their neurologic claudication and pain as well as that experienced during the early morning period of relieving tension.In cases of maladaptive treatment-related symptoms (e.g., extreme pain continuing for more than a month that does not respond to appropriate medications, disorders of urinary and fecal continence, and sudden loss of function or sensation in the lower limb), it will be necessary to proceed to surgical intervention to prevent secondary neurological damage.

*Cautionary Notes regarding Walking Training or Routine Walking *
Walking time is to be adjusted according to the conditions of the patient. However, adjustments will be required in the walking time from 10 to 20 minutes and thus patients may need to rest by suspending the exercise in cases of pain.During the first week of treatment, patients may experience symptoms in the incubation period and hence may need to rest by limiting their exercise level to the minimum.During the second week of treatment, the patients shall increase their walking distance for 20 m after two to three days depending on each patient's individual situation.After the end of treatment sessions, the patients must increase their walking time by one minute every three days for two to three months and must aim to walk routinely for approximately one half hour without pain.

*Cautionary Notes for Exercise*

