### 2.9. Data Monitoring and Dropout Criteria

Data monitoring will be conducted regularly by researchers from the Korea Institute of Oriental Medicine for fair clinical trial. Source data from the study will be handled and analyzed by an independent statistician. Patients who want to stop participating in this study, do not complete the treatment over four visits, violate the study protocol, withdraw consent for participation, and use prohibited treatments for lumbar stenosis will be dropped out from the study.

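### Additional treatment is tallied only in follow-up, while the same event in the four treatment weeks makes the patient a dropout, so the per-arm tally leans towards patients who completed the four weeks

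*Protocol article*

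**What the plan says.** Four sections of the protocol article bear on the point.

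- **Section 2.6 (Outcomes)** sets the tally and its window: "The types and frequency of additional treatments usage during follow-up period will be assessed and analyzed after the end of the study". The item is not in the list of primary and secondary outcomes that opens the section, and Table 1 has no row for it.
- **Section 2.5 (Intervention)** covers the treatment weeks: "Any concomitant therapies for lumbar stenosis will be prohibited during the four-week treatment period in all patients". Its patient education list also foresees that, for certain severe symptoms, "it will be necessary to proceed to surgical intervention to prevent secondary neurological damage".
- **Section 2.9 (Data Monitoring and Dropout Criteria)** says that patients who "use prohibited treatments for lumbar stenosis will be dropped out from the study". It gives no time limit for this rule.
- **Section 2.7 (Feasibility Assessment)** says: "Recruitment rate and dropout rate during the study period will be assessed for evaluating the feasibility of the study design", and then: "Reasons for the dropouts will be analyzed".

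Section 2.8 commits the analysis to intention to treat.

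**The concern.** Every participant has already been recommended for decompression or fusion surgery (Section 2.3). How many go on to surgery or other treatment, and in which arm, is therefore informative about a nonsurgical program and about the design of the full trial. The plan splits that information by calendar time. An event after the treatment period enters a tally by kind and number. The same event a few weeks earlier enters a list of dropout reasons kept for feasibility, and the patient may then be absent from the later tally as well.

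The split need not fall evenly across arms. Analgesics, epidural injections and physiotherapy are assigned care in the usual care arm. The same treatments are outside the program in the two Mokhuri arms and are prohibited there during the four weeks. A Mokhuri patient who receives an injection in week 3 of treatment meets a dropout criterion, whereas a usual care patient who receives one is on protocol. Read on its own, a follow-up-only figure per arm can make the arm with more early failures look better.

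**Working it through.** **Inputs.** 12 patients per group and 36 in total, with no sample size calculation (Section 2.2). Assessment weeks 0, 2, 3, 4, 5, 6, 18 and 30 (Table 1), with the four-week treatment running from week 2 to week 6. The plan gives no rate of conversion to other treatment and no figure for this tally, so there is nothing of its own to reproduce beyond 3 × 12 = 36, which agrees.

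**Step 1. Follow one event through the text.** Take surgery, or an injection that is not part of the patient's arm.

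| When it occurs | Status | Where it is reported |
|---|---|---|
| Weeks 2 to 6 | Prohibited (2.5), so a ground for dropout (2.9) | Dropout rate and reasons (2.7) |
| Weeks 6 to 30 | Additional treatment (2.6); also a dropout if 2.9 is read without a time limit | Additional-treatment tally (2.6), possibly also 2.7 |

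No section joins the two rows. The second row also contains a possible collision, because the use that Section 2.6 sets out to count could itself remove the patient under Section 2.9.

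**Step 2. Length of the uncounted window.** (6 − 2)/(30 − 2) = 4/28 = 14% of the weeks from week 2 to week 30.

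**Step 3. Size per patient.** In one arm, let E patients have their first such treatment in the treatment weeks and L in follow-up. Assume that the E patients do not contribute afterwards.

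- Whole-study proportion: (E + L)/12.
- Tally over patients randomised: L/12, a shortfall of E/12. For E = 1 this is 1/12 = 8.3 percentage points.
- Tally over patients remaining: L/(12 − E).

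With assumed values E = 1 and L = 2, the whole-study proportion is 3/12 = 25.0%. The tally gives 2/12 = 16.7% or 2/11 = 18.2%, a shortfall of 8.3 or 6.8 points.

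For two arms over patients randomised, the difference between arms is shifted by (E₁ − E₂)/12. Equal early numbers cancel, so the comparison is biased only where early conversions differ between arms.

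**Step 4. Could there be any early events?** With an assumed four-week rate r, the expected number is 36r. The chance of at least one is 1 − (1 − r)³⁶ in the trial and 1 − (1 − r)¹² in one arm.

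| Assumed r | Expected of 36 | At least one of 36 | At least one of 12 |
|---|---|---|---|
| 2% | 0.7 | 52% | 22% |
| 5% | 1.8 | 84% | 46% |
| 10% | 3.6 | 98% | 72% |
| 20% | 7.2 | over 99.9% | 93% |

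These rates are illustrations only. Inpatient care under a prohibition may keep the true rate low.

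**The case against.** The strongest reply is that early conversions do have a stated place in the results. Patients are inpatients, so such an event would be seen. Section 2.9 classes it as a dropout, and Section 2.7 analyses the reasons. It is also coherent to speak of additional treatment only once such treatment is no longer prohibited. This stands against any claim that early conversions disappear: a reader might infer a total omission, and the document does not support it. It does not answer the narrower point. Section 2.7 does not promise the kind and number of treatments, as Section 2.6 does, and nothing brings the two sources together.

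Other stronger readings also fail:

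- **Recall.** The 12-week gaps from week 6 to 18 and from 18 to 30 might suggest that later treatment is undated and rests on memory. The article states no method of ascertainment, a visit interval is not a recall period, and a condensed article commonly leaves such detail to the full protocol.
- **Reversed comparison.** One can construct counts in which the tally reverses the order of two arms, but the plan gives no rates that make this likely. Twelve patients per arm in a feasibility pilot would not support a firm comparison in any case.
- **Surgery as a named item.** Section 2.6 speaks only of additional treatments. Including surgery is a natural reading in this population, but it is a reading.
- **Collision during follow-up.** Section 2.5 limits the prohibition to four weeks, so Section 2.9 may be meant to apply only then. It does not say so, and the ambiguity remains.

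**Conclusion.** The point holds in limited form. The stated additional-treatment tally starts only at follow-up and, because of the dropout rule, may cover mainly patients who completed the four weeks. That fits poorly with the intention-to-treat commitment in Section 2.8. It is a biased tally and not a loss of all information, since the dropout reasons remain available. Each patient so omitted is worth 8.3 percentage points in an arm of 12. The comparison between arms is distorted only if early conversions differ between arms, which is plausible because the set of prohibited treatments differs by arm.

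The conclusion assumes that patients dropped under Section 2.9 may not be assessed at weeks 18 and 30. The text suggests this but does not say it outright. Severity is low: the trial is a pilot, the item is not a listed primary or secondary outcome, and the repair is small.

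**What to change.** 1. **Section 2.6:** count stenosis treatment that is not part of the patient's assigned arm, from randomisation to week 30, in all randomised patients who have not withdrawn consent to data collection. Record type and start date, and report per arm over the number randomised. The exclusion of assigned treatment is essential: Section 2.5 gives usual care patients three to four epidural injections, which would otherwise count as conversions in that arm only.
2. **Table 1:** add a matching row covering the treatment weeks and weeks 6, 18 and 30.
3. **Sections 2.6 and 2.9:** reconcile them so that stopping assigned treatment, or using other treatment, does not end outcome collection. State whether the rule in 2.9 applies after the four weeks. This concerns data collection only and leaves treatment rules to the investigators.

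The cost is wording in two sections and one table row. There is slightly more data capture at existing visits, and some effort to follow patients who have stopped treatment. No visits are added to the schedule.

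### Adverse-event capture is worded around related and unexpected events, and only the two Mokhuri arms are told to expect new week-1 symptoms, so ascertainment differs by arm and new symptoms may be under-counted there

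*Protocol article*

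**What the plan says.** **Capture rule (section 2.6, Outcomes).** "Adverse events (AEs) related to treatments will be monitored by the physicians, and patients should report any unexpected signs or symptoms during the treatment". The same section grades AEs by Spilker's classification, analyses types and frequency, and states that outcome assessors know the allocation.

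**Who receives patient education (section 2.5, Intervention).** For MT 1: "Patients in the MT 1 group will receive integrative treatments, including herbal medications, Chuna, acupuncture, and patient education". For MT 2: "Those in the MT 2 group will receive Chuna, acupuncture, and patient education without herbal medication". For usual care: "Those in the usual care group will be offered conventional nonsurgical treatments with analgesics, epidural steroid injection, and physiotherapy". The later description of usual care in the same section adds no education.

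**What the education says (section 2.5, Patient Education Information).** The General Notes advise bed rest, citing "the possibility that they will experience symptoms in the incubation period that they might not feel prior to the treatment during the first week". The walking notes repeat the message: "During the first week of treatment, patients may experience symptoms in the incubation period and hence may need to rest".

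**How AEs are used.** Section 2.8: "The frequency of AEs in each group will be compared using Fisher's exact test". Section 2.6 lists AEs as a secondary outcome. Section 3 says that the pilot's findings will feed a full-scale trial of benefits and harm.

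**When AEs are assessed.** Table 1 marks them for all participants at weeks 2, 3, 4, 5, 6, 18 and 30.

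**The concern.** A between-arm comparison of AE frequency is interpretable only if the chance that a given symptom is recorded is the same in each arm. Here the patient's reporting criterion is that the symptom be unexpected, and a component delivered in two of the three arms tells patients that new symptoms in the first week may belong to the course of treatment. An MT patient who takes that message in and follows the reporting rule literally has a reason not to report such a symptom. A usual-care patient with the same symptom has not been given that reason by anything in the article.

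The physicians' channel is worded around events related to treatment. If relatedness is used as an entry condition, it is judged by clinicians who know the arm from the treatment they give.

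At stake are the AE frequencies carried into the planning of the full-scale trial, and the between-arm AE test. An analysis plan cannot repair this afterwards, because an event that was never recorded cannot be recovered.

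**Working it through.** The plan states no AE rate, power or significance level for AEs, so there is no figure of its own to reproduce. The check is mainly textual, with an illustration on assumed rates.

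**Step 1. The provisions side by side**

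| Element | MT 1 and MT 2 | Usual care |
|---|---|---|
| Patient's criterion for reporting (2.6) | unexpected sign or symptom | unexpected sign or symptom |
| Physicians' channel (2.6) | AEs related to treatments | AEs related to treatments |
| Written message that new week-1 symptoms may occur (2.5) | yes, twice | none listed |
| Face-to-face education by the physician (2.5) | five times a week for four weeks | none listed |
| Taught weekly comparison of symptoms (2.5) | yes | none listed |
| Scheduled AE assessment (Table 1) | weeks 2 to 6, 18, 30 | weeks 2 to 6, 18, 30 |

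The rule is the same in all arms, but its key word depends on what the patient has been told, and that differs by arm. The third row pushes MT recording down. The fourth and fifth rows could push it up. All three make ascertainment unequal.

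**Step 2. Timing**

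The patient-report sentence covers the treatment period, while Table 1 continues to weeks 18 and 30. These can coexist as spontaneous reports during treatment plus scheduled assessments later. But Table 1 says when AEs are assessed, not what counts as one, and section 2.6 is the only place that describes this.

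**Step 3. What under-reporting could do (assumed rates)**

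Inputs: 12 patients per arm (section 2.2). Assumed: the same true proportion π of patients with an event in every arm; a fraction m of those events unreported in the MT arms only; two-sided 0.05. The unit is the patient with at least one recorded event.

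Expected recorded patients: usual care 12 × π; one MT arm 12 × π × (1 − m). For example, π = 50% and m = 50% give 12 × 0.5 = 6.0 against 12 × 0.5 × 0.5 = 3.0. The probability of a spurious result is the sum of binomial probabilities over all outcome tables with Fisher p ≤ 0.05 and a lower recorded proportion in MT.

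| π | m | Usual care, of 12 | One MT arm, of 12 | Spurious result favouring MT, 12 v 12 | Same, MT arms pooled, 24 v 12 |
|---|---|---|---|---|---|
| 30% | 0 | 3.6 | 3.6 | 0.9% | 1.3% |
| 30% | 25% | 3.6 | 2.7 | 2.2% | 4.7% |
| 30% | 50% | 3.6 | 1.8 | 5.4% | 14.3% |
| 50% | 0 | 6.0 | 6.0 | 1.1% | 1.5% |
| 50% | 25% | 6.0 | 4.5 | 4.7% | 6.4% |
| 50% | 50% | 6.0 | 3.0 | 14.3% | 22.2% |
| 70% | 0 | 8.4 | 8.4 | 0.9% | 1.3% |
| 70% | 25% | 8.4 | 6.3 | 7.4% | 12.6% |
| 70% | 50% | 8.4 | 4.2 | 29.3% | 41.8% |

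Pooling is shown only for range; the plan does not say that it will pool.

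Two single outcomes for scale, with 8 of 12 truly affected in each arm: if 4 of the 8 go unreported in one MT arm, the comparison is 4/12 against 8/12, p = 0.220; if 6 of the 8 do, it is 2/12 against 8/12, p = 0.036.

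In every row the spurious test is less likely than not. The more dependable effect is on the frequencies themselves: with half of the MT reports lost, the recorded MT frequency is half the true one.

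**The case against.** A reader might infer that AE recording is limited to related and unexpected events, and that harms therefore will be under-counted in the experimental arms. The documents do not support that.

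- **Limited to.** The patient channel is not restricted by relatedness, and Table 1 adds scheduled AE assessment in all participants to week 30. The rule also does not say that relatedness is judged first or that unrelated events are discarded. The statement about open assessment concerns outcome assessors and does not identify them with the monitoring physicians. All of this stands.
- **Will be under-counted.** Contact with the physician five times a week, taught weekly symptom comparison and a list of alarm symptoms could raise detection in the MT arms. An expectedness filter could also drop foreseeable drug or injection effects in usual care. What usual-care patients are told about side effects is not shown. The education speaks of a possibility, and a patient may read unexpected simply as untoward. This stands too: the net direction is open.
- **Early worsening would be missed.** Only in part. Table 1 schedules back and leg pain, the Oswestry index, EQ-5D and pain-free walking at every treatment-period time point in all arms. What is exposed is new symptoms outside those scales.
- **It is a pilot, and the article is a condensation.** Section 2.1 concerns the feasibility of trials on effectiveness and safety, and no decision in the article rests on the AE test. Form wording, and whether patients or events are counted, may be settled elsewhere. This lowers the stakes, but it does not answer the point that the rule the article does state interacts with the arm-specific education.

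The points about contact and about usual care settle the direction, not the inequality. They are further reasons to use one unfiltered rule in every arm.

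**Conclusion.** The point holds as a risk of differential ascertainment. The capture rule is worded around relatedness and expectedness, only the MT arms are told in writing to expect possible new week-1 symptoms, and AE frequencies are then compared between arms. New symptoms may be under-counted in the MT arms; neither the size nor the net direction of the difference can be derived from the documents.

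The figures are illustrations. They assume equal true rates of 30% to 70% and under-reporting of 25% to 50% in the MT arms only. Under those assumptions the chance of a spurious significant result in favour of MT in a 12-versus-12 comparison is about 2% to 7% with 25% under-reporting and 5% to 29% with 50%, against about 1% with none.

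The change should be made: it is cheap, and the loss could not be corrected at analysis.

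**What to change.** In section 2.6, replace the capture rule with one that:

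1. records every new or worsened sign or symptom in all three arms, regardless of expectedness or judged relatedness;
2. states explicitly that symptoms attributed to the incubation period are recorded as AEs;
3. elicits events with the same standard question, in every arm, at each AE visit in Table 1 through week 30;
4. records relatedness afterwards, as a separate field.

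The content of the education and the treatments need not change for this.

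Cost: a wording change and one question plus one field on the case report form. The small downside is a higher reported AE count in every arm.
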